#### Diet

4.7.2

Nutritional variables will be a highly relevant source of variance in the study, particularly for metabolome and microbiome parameters. Food compounds, energy and nutrient intake will therefore be analysed from food frequency data by the nutritional software nut.s ^®^v1.32.95 (110). Nutrient intake will be adjusted for total energy intake, and nutrients with excessive missings will be excluded.

It appears inadequate to consider dietal factors merely as control variables, as nicotine is known to interact strongly with regulation of appetite and satiety, and smoking cessation usually goes along with a weight-gain (111). Nutritional variables are therefore candidate mediator or explanatory variables, and it is important to quantify how much of the group effects will be explained by energy intake and nutrients. For this purpose, the variance explained by nutrition will be quantified via Partial distance-based redundancy analysis (db-RDA) and/or PERMANOVA (for both microbial beta diversity and metabolite distances). Variance will be decomposed by stepwise separation of variance explained by group, variance explained by nutritional variables (energy, nutrients, selected compounds), control variables (see below), and shared variance.

Additional adjustment analyses will be performed in candidate biomarkers of smoking cessation group effects emerging from metabolome and microbiome analyses (at the level of metabolites, or specific bacterial taxa). Linear mixed effects models (lme4 package in R (112)) will be iteratively tested (total effect vs. nutrition-adjusted models) for shrinked coefficients of group effects for this purpose.

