#### Controlling for potentially confounding variables, and multiple testing

4.7.3

Proper analysis of the research questions in the SUD sample will be hampered by several sources of variance, such as diet, psychiatric diagnoses, medications, and history of substance misuse. These variables will be held constant as control variables.

Psychiatric comorbidity is highly present in the population. Psychiatric symptom burden and classes of psychiatric diagnoses are associated with systematic metabolic and microbiome profiles (72, 113, 114). Classes of psychiatric secondary diagnoses (mood, anxiety, psychotic, and neurodevelopmental disorders) will therefore be considered as covariates. Intake of psychotropic medications are respectively frequent. The literature shows reciprocal interactions between psychotropic medications and gut microbiota (115), and metabolic patterns in response to treatment (116, 117). Type of medication class intake (antipsychotics, antidepressants, antianxiety drugs, anticonvulsants/mood stabilisers, opioid substitution) will be considered as covariates. Length and consumption patterns from SUD history will also enter covariate analysis (with regard to substances – primarily consumed substances vs. polytoxicomania). These covariates will be entered in Multi-omics factor analysis (MOFA) in direct joint modeling (118) to ensure that observed microbiome–metabolome–psychological associations are not driven by covariate effects. For the microbiome domain, intervention vs. control group comparisons regarding microbial abundance and composition will be performed with Analysis of Compositions of Microbiomes with Bias Correction (ANCOM-BC), a package which allows for continuous and categorical covariate adjustment within a linear regression framework, and was designed to analyze longitudinal data (119).

Metabolome and microbiome studies involve the examination and statistical testing of a multitude of variables. Thus, controlling for multiple testing is a must; False Discovery Rate corrections will be based on statistical recommendations promoting flexible algorithms within the R package FDRestimation (120).

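### Section 4.7.3 holds diet constant as a control variable, but 4.7.2 treats it as a candidate mediator and one diet record falls after randomisation

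*Protocol article*

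**What the plan says.** Section 4.7.2 (Diet) opens its argument with "It appears inadequate to consider dietal factors merely as control variables". Its reasons are that nicotine acts on appetite and satiety, and that "smoking cessation usually goes along with a weight-gain". It concludes: "Nutritional variables are therefore candidate mediator or explanatory variables". The variance decomposition in the same section lists "variance explained by nutritional variables (energy, nutrients, selected compounds), control variables (see below), and shared variance", so nutrition and the control variables are separate components. For candidate biomarkers that have already shown a group effect, it then compares mixed models with and without nutrition and looks for shrinkage of the group coefficient.

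Section 4.7.3, the section that 4.7.2 points to for the control variables, says the analysis will be "hampered by several sources of variance, such as diet, psychiatric diagnoses, medications, and history of substance misuse". The next sentence is "These variables will be held constant as control variables". It makes no exception for diet and does not say which diet record is meant.

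**The concern.** Section 4.7.2 places diet on the pathway from cessation to the biological outcomes; 4.7.3 places it among the nuisance variables to be held constant. In a randomised comparison these roles call for different models. A baseline covariate can be adjusted for without changing the effect being estimated. A variable measured after allocation and affected by it cannot: conditioning on it gives an arm effect with that pathway removed.

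At stake are the metabolome and microbiome arm comparisons that take covariates. If screening followed 4.7.3 literally, a marker that changes because cessation changes eating would be weakened or lost at the screening stage. The step in 4.7.2 that reports the effect with and without nutrition would not recover it, because that step starts from biomarkers already found.

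**Working it through.** No figure in the protocol has to be reproduced. The check compares the sections, then shows what the literal reading of 4.7.3 would do.

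**1. Role of diet.** In 4.7.2 it is a candidate mediator or explanatory variable, separate from the control variables. In 4.7.3 it is first in the list of variables to be held constant. Section 4.7.7 refers the reader to both sections and does not settle the matter.

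**2. Timing.** Section 4.4.2 has participants record food intake in the week before the blood and stool assessments. Section 4.1 and Table 1 place biological sampling at baseline and after 6 weeks. Section 4.2 places random assignment before the programme starts. The 6-week diet record is therefore post-randomisation, and by the reasoning of 4.7.2 it may be affected by allocation.

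**3. Where adjustment could happen.** Section 4.7.3 plans the microbiome arm comparison with ANCOM-BC and notes that the method accepts continuous and categorical covariates.

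**4. Effect of adjusting.** Take a linear model in SD units, with *a* the arm effect on diet, *b* the diet effect on the marker and *c* the direct effect:

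- total effect = c + a·b
- mediated share s = a·b / total
- arm coefficient with post-randomisation diet in the model = c = total × (1 − s)

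The last line assumes no unmeasured causes shared by diet and marker; if there are any, adjustment adds further bias. The shares below are assumptions. The total of 0.70 is only a round illustration, the size the power section gives for self-efficacy.

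| Assumed share s | 0.70 × (1 − s) | Simulated, adjusted for 6-week diet | Simulated, adjusted for baseline diet |
|---|---|---|---|
| 0% | 0.70 | 0.71 | 0.71 |
| 10% | 0.63 | 0.63 | 0.70 |
| 25% | 0.525 | 0.53 | 0.70 |
| 50% | 0.35 | 0.35 | 0.70 |

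The simulation used 46 per arm, 3,000 replicates, a = 0.5 SD and a correlation of 0.5 between baseline and later diet. Adjusting for baseline diet leaves the total effect intact at every share.

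**5. Why no power figure is given.** Power depends on a second unknown, the arm effect on diet. Take 45 per arm (100 × 0.9 / 2, from the planned 100 and 10% attrition), a total of 0.70 and a 30% share, so that the adjusted coefficient is 0.49. The same linear model then gives power of 0.89, 0.69 or 0.62 for an arm effect on diet of 0.3, 0.5 or 0.7 SD. The documents do not narrow that range.

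**The case against.** The best defence is that the plan does not actually put diet into the arm models. Where 4.7.3 specifies its covariates, it names diagnosis classes, medication classes and substance use history, and these are what enter MOFA; diet is not repeated. ANCOM-BC is said to allow covariates, but no diet term is assigned to it. Section 4.7.2 already compares group effects with and without nutrition. Its wording, that diet is inadequate merely as a control, leaves room for two roles. All of this stands and limits the finding. It does not cancel the sentence in 4.7.3, which leaves a reader unable to tell whether diet enters, or which record.

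Three stronger readings are tempting, and the documents do not support them:

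- *All biological arm effects will be attenuated.* Several arm tests are described without covariates: Kruskal-Wallis for alpha diversity and LEfSe (4.7.5), and the univariate plasma metabolite tests (4.7.6.3). The psychological ANOVA and GEE in 4.7.4 name no diet term.
- *A particular loss of power follows.* The mediated share is not given, 4.7.7 says meals are shared, and section 2 calls the investigations largely exploratory.
- *The stepwise variance decomposition is invalid because it depends on entry order.* Section 4.7.2 names partial db-RDA and reports shared variance as its own component, which largely answers this.

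**Conclusion.** The concern holds as an inconsistency between two adjacent sections, with a real but conditional consequence. As worded, 4.7.3 permits post-randomisation diet to be held constant in covariate-adjusted arm comparisons of microbiome and metabolome outcomes. Such a comparison would not estimate the total effect of allocation. The part lost equals the diet-mediated share under a linear model without unmeasured common causes, and it is nil if cessation does not change intake or intake does not change the marker. The size cannot be fixed from the documents. The total effect is not lost throughout the plan; the exposure is at the screening step for models that take covariates.

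**What to change.** In 4.7.3, either remove diet from the variables to be held constant or restrict it to the baseline, pre-randomisation record. Section 4.2 mentions allocation before it describes sampling, so the wording should tie that record to a point before allocation. Add one sentence stating that the main arm effect on biological outcomes is not adjusted for post-randomisation diet. Keep the nutrition-adjusted models and the variance decomposition of 4.7.2 as they are, labelled as the exploratory mediation analysis. The cost is wording in two sections; data collection does not change.

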**Methods:**

A randomized controlled trial (N = 100) will be conducted, examining outcomes such as clinical relapse rates as well as microbial and metabolic markers, investigating pathways of short-chain fatty acids, oxidative stress and inflammation, lipid, tryptophan, and one-carbon metabolism. Participants will undergo a CBT smoking cessation intervention, with pre- and post-assessments, compared to a control group receiving treatment as usual. Metabolomic and microbiome analyses will be conducted using blood and stool samples, alongside psychological assessments via questionnaires. Covariate analyses will be undertaken to control for metabolic and gut microbial effects of long-term psychiatric medications (antidepressants, mood stabilizers, antipsychotics, and opioid substitutions) present in the sample. Behavioral assessments will be conducted at a 3-month follow-up. The study is registered at clinicaltrials.gov under NCT06803706.

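### Entering the covariates in MOFA by joint modelling does not condition on them, so the assurance given for the exploratory cross-domain associations is not delivered

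*Protocol article*

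**What the plan says.** Section 4.7.3 lists diet, psychiatric diagnoses, medications and history of substance misuse as sources of variance and states: "These variables will be held constant as control variables". It then defines three blocks.

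- Diagnoses: "Classes of psychiatric secondary diagnoses (mood, anxiety, psychotic, and neurodevelopmental disorders) will therefore be considered as covariates".
- Medication: "Type of medication class intake (antipsychotics, antidepressants, antianxiety drugs, anticonvulsants/mood stabilisers, opioid substitution) will be considered as covariates".
- History: "Length and consumption patterns from SUD history will also enter covariate analysis".

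For the associations that run across microbiome, metabolome and psychology, one mechanism is named: "These covariates will be entered in Multi-omics factor analysis (MOFA) in direct joint modeling". The reason given is "to ensure that observed microbiome–metabolome–psychological associations are not driven by covariate effects". The section states no regressing-out, no conditioning step and no rule for factors that load on a covariate.

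The section also gives grounds for expecting confounding: "Psychiatric symptom burden and classes of psychiatric diagnoses are associated with systematic metabolic and microbiome profiles". It describes psychotropic medication as frequent and as related to both gut microbiota and metabolic patterns.

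**The concern.** The plan names a method and a property that the method is meant to deliver. Multi-omics factor analysis looks for factors that explain variance shared by whatever is entered. If a drug class shifts a taxon, a metabolite and a symptom score, entering the drug class yields a factor that loads on all four. The taxon–metabolite–symptom association is then described, with the drug as a companion; it is not held constant.

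At stake is how the cross-domain results are read. The abstract hypothesises that metabolic and microbiome changes mediate the psychological effects. Sections 2.1.2 and 2.1.3 set out to find biological correlates of emotions and symptoms. Randomisation does not protect such within-sample associations, and a reader of section 4.7.3 would take them as already adjusted for medication and diagnosis.

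**Working it through.** The plan gives no figure on this point, so there is none to reproduce.

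**Step 1. Does another step supply the adjustment?**

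- ANCOM-BC (4.7.3) adjusts for covariates by regression, but for intervention-versus-control comparisons of microbial abundance and composition.
- db-RDA/PERMANOVA (4.7.2) splits the variance of microbial and metabolite distances into group, nutrition, control-variable and shared parts. It does not adjust an association between domains.
- The mixed models in 4.7.2 compare group effects with and without nutrition.
- Table 2 (4.7.4) gives correlation and regression for cross-domain associations. It names no covariates and does not list MOFA.

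None of these adjusts the cross-domain associations.

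**Step 2. Algebra.** Let x = b·c + e and y = b·c + e′, with covariate c of variance 1, independent noise of variance 1, and no direct link between x and y. Then corr(x, y) = b²/(1 + b²), and the correlation given c is 0.

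- b = 0.6: 0.36/1.36 = 0.265.
- b = 0.4: 0.16/1.16 = 0.138.

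A factor model fitted to x, y and c together finds a factor close to c. Each feature loads b/√(1 + b²) on it, so the model-implied correlation is again b²/(1 + b²). Entering c labels the factor but does not remove the association.

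**Step 3. Simulation.** From the plan: N = 100 (4.7.1). Assumed: ten binary covariates at 40% prevalence, one active unless stated; two omics views of 30 features and six psychological items, half of each affected; three factors unless stated; 200 replicates. A maximum-likelihood factor model stood in for MOFA, without its sparsity priors. The table gives the model-implied microbiome–psychology correlation; the correct conditional value is 0.

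| Scenario | No covariates | Covariates entered | Residualised first |
|---|---|---|---|
| b = 0.6 | 0.265 | 0.269 | -0.001 |
| b = 0.4 | 0.138 | 0.142 | -0.001 |
| b = 0.6, three active covariates | 0.268 | 0.270 | 0.001 |
| b = 0.6, six factors | 0.263 | 0.266 | -0.001 |

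A second stand-in, a one-factor singular value decomposition, agrees. Assumed inputs: n = 90, one drug in 40%, 1 SD effect on 20 taxa and 20 metabolites, 300 data sets. The raw correlation was 0.192 (formula: 0.4 × 0.6 = 0.24; 0.24/1.24 = 0.194). The factor-implied correlation was 0.2096 without the covariate and 0.2099 with it. After residualising, the cross-correlation was 0.0005.

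**Step 4. Would dropping the covariate-loaded factor rescue it?** The plan does not state this step. It was tested with b = 0.6 and 150 replicates. The target is the value after residualising.

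| Scenario | Covariates entered | Factor dropped | Target | Correlation of factor with covariate |
|---|---|---|---|---|
| Covariate is the only driver | 0.269 | -0.001 | -0.001 | 0.997 |
| Genuine factor, separate features | 0.269 | 0.047 | -0.001 | 0.906 |
| Genuine factor (0.6), overlapping features | 0.419 | 0.393 | 0.265 | 0.854 |
| Genuine factor (0.4), overlapping features | 0.345 | 0.053 | 0.139 | 0.766 |

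The covariate shows up clearly, but dropping its factor under-corrects in one overlapping case and over-corrects in the other.

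**Step 5. Levels or changes.** The article does not say which MOFA will use. If the covariate effect is constant and additive, b·c cancels in post minus pre and the spurious correlation is 0. A run of the n = 90 set-up on changes gave -0.0004.

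**The case against.** The article does not spell out the MOFA implementation. It cites a source that is not at hand, and pre-processing is the sort of detail a condensed article leaves out. That the covariates go in as data alongside the omics views is therefore a reading, though the natural one for joint modelling. An analyst would also be likely to notice the problem: the leading factor correlated 0.77 to 1.00 with the covariate, and removing it worked when nothing else was going on. The design is pre-post, and section 4.5 requires stable dosage of long-term medication for at least three months before inclusion, so an analysis of changes would be far less exposed. Section 2 calls the work largely exploratory, and Table 2 labels the cross-domain associations so.

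All of this limits the size and reach of the point. It does not rescue the assurance: visibility is not adjustment, the rule for acting on what is seen is unstated and was unreliable in step 4, and exploratory status does not justify a guarantee.

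A reader might also infer that the abstract is wrong where it says "Covariate analyses will be undertaken to control for metabolic and gut microbial effects of long-term psychiatric medications". It is not. That sentence promises covariate analyses without naming MOFA, and sections 4.7.2 and 4.7.3 describe such analyses for both biological domains.

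**Conclusion.** The point holds, within limits. On the natural reading of section 4.7.3, the named step does not condition on the covariates. Freedom from covariate effects is therefore not ensured for the microbiome–metabolome–psychological associations.

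The illustrative size is a spurious correlation of about 0.14 to 0.27 that entering the covariates leaves unchanged and conditioning reduces to about 0. It rests on assumed prevalence and effect sizes, on stand-ins for MOFA, and on an analysis of levels. For changes under stable medication it would be smaller, down to about 0 if the effect is constant and additive.

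Two stronger readings are tempting and not supported. One is that the reported associations would be false: that holds only where a covariate does drive one, which the plan's own premise makes plausible but does not show. The other is that the trial's group comparisons are compromised: randomised contrasts are not confounded by baseline covariates in expectation, and ANCOM-BC adjusts explicitly.

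**What to change.** Replace the MOFA sentence in section 4.7.3 with wording to this effect: cross-domain associations will be adjusted for baseline medication class, substance-use history and sex, either by residualising the views on these variables before MOFA or by including them in the regressions of factor scores and of feature pairs; MOFA with covariates entered, and factor–covariate correlations, will be reported as a diagnostic only; the adjustment reduces confounding by the measured covariates. State whether levels or changes are analysed, and carry the same covariates into the cross-domain row of Table 2.

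Report results with and without adjustment for psychiatric diagnosis class. Mood and anxiety diagnoses overlap with the depressive and anxiety scales of the symptom questionnaire (4.4.1), and correlates of symptoms are a study aim. Name the covariates explicitly, because section 4.7.3 also lists diet among the variables to be held constant. Diet is measured after randomisation as well as before, and section 4.7.2 treats it as a candidate mediator, so post-randomisation diet should not be residualised out.

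The cost is a few lines of code and text, plus degrees of freedom. Five medication classes, sex and at least one term for history make 7; four diagnosis classes bring it to 11. It is more if length and pattern of use take separate terms. This is at 100 participants, or about 90 after the planned 10% attrition. Adjusting for diagnosis also removes some of the symptom variance under study, hence both versions.

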#### Statistical analyses of psychological variables

4.7.4

The statistical analyses will be performed in SPSS version 29 (IBM) for general procedures, while specific regression models are handled in R (R core team (121)). For example, t-tests will be carried out for independent and paired comparisons of means between and within groups at different times, respectively, assuming that the continuous data are normally distributed. Chi-square and Fisher’s exact tests, the latter in cases of smaller sample sizes, will be conducted in order to test the associations between categorical variables. The Friedman test shall be used in analyzing non-parametric repeated measures. The main effects of the intervention, time effects, and group x time interaction will be tested using a 2 × 3 two-way repeated measures ANOVA design (group x time), using the Greenhouse-Geisser correction in cases when the sphericity assumption will be violated. The level of significance will be α = 0.05, two-tailed, using Bonferroni adjustment for multiple comparisons. In addition, a repeated measures proportional odds logistic regression model using a generalized estimating equation (GEE) will be applied, assessing the intervention’s effect on CPD treated as an ordinal variable. The GEE model, computed in R using the `repolr` package (122), will contain robust variance estimators that take into account within-subject correlations (**Table 2**).

**Table 2 T2:** Summary of statistical methods and outcomes.

Outcome variable	Domain	Statistical method	Software
Self-efficacy, craving, psychiatric scores	Psychobehavioural	Repeated measures ANOVA, t-tests, Friedman test	SPSS
Cigarettes per day (ordinal)	Psychobehavioural	GEE (Proportional odds model)	R (repolr)
Bacterial diversity indices	Microbiome	Kruskal-Wallis, ANOSIM, db-RDA	R, QIIME
Taxonomic composition	Microbiome	MaAsLin2, ANCOM, LEfSe	QIIME2, R
Metabolite concentrations	Metabolic	PCA, O-PLS-DA, correlation analyses	NMR tools, R
Cross-domain associations	Combined (exploratory)	Correlation and regression	R

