### Type and design of the study

4.1

The present study is a randomized controlled experiment in N = 100 SUD- inpatients during a therapeutic community treatment with one intervention group that will receive an additional 6-week smoking cessation intervention and one control group that will receive treatment as usual. The study design consists of a 2 x 2 mixed subject design with repeated measures for the biological analyses and a 2 x 3 mixed subject design with repeated measures for the psychobehavioural analyses (see **Table 1**). In both groups, an examination of metabolic and gut microbial profiles, as well as psychological variables, will take place. Biological parameters will be ascertained from blood and stool specimens for nuclear magnetic resonance (NMR) spectroscopy metabolomic analyses and from stool specimens for 16s-mRNA (hypervariable V3-V4 regions) sequencing and subsequent gut microbial profiling. Psychobehavioural and biological data will be collected pre & post smoking cessation, and additionally, there will be a follow-up measurement of the psychobehavioural variables 3 months upon completion of the study (see **Figure 3**: Consort Flow Chart for further illustration).

**Table 1 T1:** Overview of the statistical design.

Study group	Pre- intervention baseline	Post- intervention after 6 weeks	Follow- up after 3 months
Intervention Group (N = 50)	Psychobehavioural Data	Psychobehavioural Data	Psychobehavioural Data
	Metabolic/Microbial Data	Metabolic/Microbial Data	
Control Group (N = 50)	Psychobehavioural Data	Psychobehavioural Data	Psychobehavioural Data
	Metabolic/Microbial Data	Metabolic/Microbial Data	

green cells: biological data; light brown cells: self-report data.

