#### Psychobehavioural variables – psychometric measures

4.4.1

In addition to anamnestic data, the following previously validated instruments showing good psychometric properties will be applied:

Self-efficacy: The Self-Efficacy Scale (SWE (100)) is a self-report instrument for measuring general optimistic self-confidence. It consists of 10 items and measures optimistic competence expectancy, i.e., confidence in solving difficult situations with one’s own abilities.

General substance related craving: The MaCS (Mannheim Craving Scale (101)) is an instrument for measuring substance related craving. It consists of 12 items and four additional items and is rated on a 5-point Likert scale.

Tobacco dependence: The Fagerström Test for Cigarette Dependence (formerly Fagerström Test for Nicotine Dependence; FTND (102)) is a self-assessment instrument measuring tobacco dependence intensity. It consists of 6 categorically scaled items that assess the number of smoked cigarettes per day (CPD), compulsive use, and dependence intensity.

Psychiatric Symptoms: For the evaluation of psychopathology, the ICD-10 Symptom Rating (ISR (103)) questionnaire was utilized. In accordance with the ICD-10, this self-assessment questionnaire, comprising 30 items, is designed to comprehensively assess the status and severity of mental disturbances. Symptoms of the six symptomatic patterns – depressive, anxiety, obsessive-compulsive, eating disorders, somatoform syndrome, and post-traumatic stress disorder – are assessed.

Primary Affects: The German version of the Brief Affective Neuroscience Personality Scales including a LUST Scale (BANPS–GL (104)) is a self-report questionnaire to measure all seven primary affects proposed by Jaak Panksepp (105) as personality traits.

Smoking behaviour: As previously in the pilot study, participants will be asked regarding their daily smoked cigarettes in the last two weeks (interval scaled). A second, dichotomous single-item question will assess if participants have been completely abstinent from tobacco smoking in the last two weeks.

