A-priori sample size calculations were performed with G-Power (108) (version 3.1.9.6), for a mixed-design ANOVA with one interaction between group (2 groups) and assessments (2 repeated measurements). Considering the effects mentioned above, the mixed-design ANOVA was set rather conservatively for a medium effect size (Cohen’s F = 0.25), a statistical Power (1-β) of 0.9, a α of 0.05, an intra-correlation coefficient of 0.5 and nonsphericity correction of 1, resulting in a minimum sample size of 46 subjects per group, and a critical F = 4.06. Adjusting for expected attrition of about 10%, a total sample size of size of 100 is set. The many (mostly biological) variables measured in this study will expectably require statistical corrections; this will also be compensated by statistical methods exceeding classical linear approaches, namely machine learning feature detection and modelling methods (109).

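### Naming Boschloo's exact test in place of Fisher's as the small-count fallback would add about 7 to 12 points of power if abstinence is rare overall; this is a cheap improvement, not an error

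*Protocol article*

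**What the plan says.** Section 4.7.4 names two tests for associations between categorical variables: "Chi-square and Fisher’s exact tests, the latter in cases of smaller sample sizes". It does not say what sample size or expected count triggers the switch to Fisher. The same section sets the level: "The level of significance will be α = 0.05, two-tailed, using Bonferroni adjustment for multiple comparisons". The number of comparisons is not given. General procedures are to run in SPSS and specific regression models in R.

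The dichotomous outcome most clearly concerned is in section 4.4.1: "A second, dichotomous single-item question will assess if participants have been completely abstinent from tobacco smoking in the last two weeks". Table 2 does not list this item; its smoking row covers cigarettes per day, analysed by GEE. No section assigns the abstinence item to a test by name.

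Table 1 plans 50 patients in each arm. On losses, section 4.7.1 says: "Adjusting for expected attrition of about 10%, a total sample size of size of 100 is set".

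**The concern.** Section 4.3 makes complete cessation, in preference to gradual reduction, the aim of the programme. A yes/no comparison of abstinence between arms is therefore a natural analysis, and chi-square and Fisher are the only tests the article offers for it. Fisher conditions on the total number of abstainers. When that total is small, few tables are possible, so the attainable error rate falls well below the nominal 5% and power falls with it.

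Boschloo's test takes the Fisher p-value as its statistic. It raises the cut-off until the maximum error rate over all common rates just stays within 5%. For two independent arms it rejects every table that Fisher rejects, and some more. What is at stake is power in one secondary comparison, and only when the outcome is rare. Validity is not in question.

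**Working it through.** **Plan's own figure.** The article gives no power figure for a dichotomous outcome, so there is none to reproduce. Its one sample-size calculation is for the group by time interaction in an ANOVA and does not enter below.

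**Inputs from the document.** Two-sided α = 0.05 (section 4.7.4); 50 per arm (Table 1); about 10% attrition (section 4.7.1), so 50 × 0.90 = 45 per arm analysed.

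**Assumed inputs.** The abstinence rates, shown as a range. The switching rule: Fisher if the smallest expected count is below 5, otherwise uncorrected chi-square. No Bonferroni division.

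**Method.** Enumerate all 46 × 46 possible tables (x abstainers in one arm, y in the other). Size at common rate p is the sum of Bin(x; 45, p) × Bin(y; 45, p) over rejected tables. Power replaces the two p's by p1 and p2. For Boschloo, reject when the two-sided Fisher p-value is at most c, where c is the largest value that keeps the maximum size within 0.05. This gives c = 0.075 at 45 per arm and 0.069 at 50 per arm.

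**When Fisher is reached.** With equal arms the smaller expected count is (x + y)/2. It is below 5 only if x + y < 10, that is, fewer than 10 abstainers in both arms together. (The mirror case, fewer than 10 non-abstainers, is not relevant at these rates.)

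**Size at 45 per arm, in percent:**

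| Common rate | Fisher on every table | Boschloo on every table | Mixed rule (Fisher / chi-square) |
|---|---|---|---|
| 3% | 0.11 | 0.58 | 0.12 |
| 5% | 0.57 | 1.8 | 0.64 |
| 10% | 2.0 | 3.4 | 3.4 |
| Maximum over all rates | 3.2 | 4.9 | 5.4 |

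At 50 per arm, Fisher's size is 0.17%, 0.72% and 1.8% at the same three rates, with a maximum of 3.5%. With Boschloo in place of Fisher in the small-count branch, the mixed rule still peaks at 5.4% (45 per arm). The excess over 5% comes from the chi-square branch.

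**Power at 45 per arm, mixed rule, before and after replacing Fisher by Boschloo in the small-count branch only:**

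| Abstinent, control vs intervention | Fisher branch | Boschloo branch | Gain (points) | Chance the branch is reached |
|---|---|---|---|---|
| 2% vs 12% | 27.5% | 39.6% | 12 | 91% |
| 2% vs 15% | 47.7% | 59.2% | 12 | 77% |
| 4% vs 15% | 34.2% | 41.2% | 7 | 65% |
| 5% vs 20% | 57.0% | 60.4% | 3 | 29% |
| 5% vs 25% | 79.4% | 80.7% | 1 | 11% |
| 10% vs 30% | 69.3% | 69.4% | 0 | 1% |

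At 50 per arm the first two rows become 34.8% to 46.3% and 56.7% to 66.5%.

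**A table that shows the difference.** With 5 abstainers vs 0 at 45 per arm, the two-sided Fisher p is 2 × C(45,5)/C(90,5) = 2 × 1,221,759 / 43,949,268 = 0.056. Fisher does not reject; Boschloo does, since 0.056 < 0.075. The same holds for 7 vs 1, where the Fisher p is 0.058. With no abstainers among controls, Fisher needs 6 in the intervention arm and Boschloo needs 5.

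**The case against.** The strongest reply is that chi-square with a Fisher fallback is conventional and valid, that the article says nothing wrong here, and that the exact test for one secondary item is ordinary detail. That stands: this is an efficiency remark.

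A reader might also infer several stronger things that the document does not support:

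- *That abstinence will be tested by Fisher.* No section says so. The trigger is undefined, and the expected-count rule used above is an assumption.
- *That few quitters among controls are enough to cause the loss.* Under that rule the total across both arms must be below 10. Once the intervention arm reaches 20% to 25%, Fisher is seldom used and the gain nearly disappears.
- *That abstinence will be rare.* No rate is assumed for this trial. Every participant must want to quit, and the programme adds recommendations on nicotine replacement. The only abstinence figure, 14 of 26 in a cited cessation study (section 4.7.1), is far above the range where Fisher matters. Section 3.1 places that study among those in patients without SUD, so it is a weak guide, but it does not point to low counts.
- *That the plan's error rate is 0.1% to 2%.* That is Fisher applied to every table. At a common rate of 10% the mixed rule has size 3.4%.
- *That the power gains come with an exact 5% guarantee.* Boschloo used alone has that guarantee (maximum 4.9%); the mixed rule does not, before or after the change. Nor does Boschloo used on every table always beat the mixed rule: at 5% vs 20% it has 55.2% power against 57.0%. The statement that power never falls applies to replacing Fisher within the small-count branch.

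The Bonferroni adjustment is a further limit. At a stricter level all these figures change, and the number of comparisons is not stated.

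**Conclusion.** The point holds as a low-cost improvement and not as an error in the plan. If a dichotomous outcome such as two-week abstinence is compared between arms and turns out rare in both, Fisher gives up power that Boschloo recovers: about 7 to 12 points for control rates of 2% to 4% against 12% to 15%. The gain is about 3 points at 5% vs 20%, 1 point at 5% vs 25%, and nil at 10% vs 30%. These sizes rest on 45 per arm, an unadjusted two-sided 5% level, an assumed expected-count threshold of 5, and abstinence rates that the document does not give. If abstinence is common, nothing is lost by the present wording and nothing is gained by changing it.

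**What to change.** In section 4.7.4, for two-arm comparisons of dichotomous outcomes with small expected counts, name Boschloo's exact unconditional test in place of Fisher's. State the expected-count threshold at the same time. Fix the choice before any results by arm are seen, because turning to Boschloo after a Fisher p of 0.056 would not be credible. If a guaranteed 5% level is wanted whatever the counts, use Boschloo for the whole comparison, accepting slightly lower power than the mixed rule at rates such as 5% vs 20%.

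The cost is one phrase in the text and one line of code. The test would run in R, which the plan already uses, and not in SPSS, which it assigns to general procedures. No extra data or patients are needed.
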